**Fig. 1 Fig1:**
[figure not shown]
Research process

### Setting and participants

The intervention will take place in Tehran, the capital of Iran. Samples from the control and intervention groups will be selected from the Primary Health Center (PHC). Participants will be 30 couples who have been married for at least 2 years or more and have not been diagnosed with infertility. The couple's infertility will be determined based on their previous medical records available at medical centers.

### Inclusion criteria

Aged from 18 to 40 years old for women and up to 45 years old for men, want to participate in research, being in the pre-contemplation or contemplation stage, married for 2 years or more, no contraindications to pregnancy, have no history of infertility, use of contraceptives, have no mental disability that interferes with learning.

### Exclusion criteria

Unwillingness to participate in the study, not attending more than one session, diagnosed infertility, or any chronic disease contraindicated for pregnancy.

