**Methods:**

Thirty couples (intervention, n = 15; control, n = 15) will be enrolled in this cluster randomized controlled trial. After collecting baseline data and separating participants in the pre-contemplation and contemplation stages based on the TTM, the samples were randomly assigned to the intervention and control groups. The intervention group will receive 60-min training based on TPB components for 4 weeks. The first follow-up assessment was performed immediately after the intervention and the final assessment 6 months later. For all 3 time assessments, three questionnaires will be used: The knowledge questionnaire, the TTM, and the TPB questionnaire. The most important consequences are changes in knowledge, attitudes, subjective norms, perceived behavioral control, and stages of intentions to have children.

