### Interventions

After receiving the ethical code from the Research Center of Tehran University of Medical Sciences, the study will begin. The educational content of this study will be prepared under the supervision of specialized professors of the university and the researcher will acquire the necessary knowledge and skills to carry out the educational program under the supervision of professors. In preparing this content, we will try to include the following: Complications due to reduced population growth, factors affecting the reduced ability to have children, effects of reduced population growth on family and society, complications of pregnancy at older ages, effects of father's age, benefits of having children, economic effects of demographic decline. The choice of the content is based on: the educational needs of the couples reflected in the studies, the cultural problems of the society, and the subjects mentioned by the Ministry of Health of Iran. After the teaching materials are prepared, their contents are scientifically evaluated by the Tehran University of Medicine professors, and after their approval, the intervention and training process will begin. Teaching classes will be conducted in 4 sessions and each session will last at least 60 min with the presence of couples (Table 1).

**Table 1 Tab1:** The content of the educational sessions based on the theory of planned behavior

session	Main purpose	Educational materials	Educational methods and time schedule
1	Improving couples’ knowledge and attitudes toward	PowerPoint Booklet (including contents of all sessions) Pamphlet of the first session	1) Introducing presenter and participants and explaining study aims (10 min) 2) Giving information on effect of advanced ages on fertility capacity of couples and the pregnancy’s complications (40 min) 3) Question and answer (10 min)
2	Addressing the role of subjective norms in childbearing	PowerPoint Pamphlet of the second session	1) Reviewing previous session (5 min) 2) Giving information related to Islamic beliefs on childbearing and the importance of having a child on the religious and social perspectives of Iran (15 min) 3) Presenter will use the psychodrama method. In this method two female volunteer who have at least one child role‐play problems and release their intense emotions in regard to the child, then the presenter will guide their subjective norms (37) (30 min) 4) Question and answer (10 min)

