### Sample size

To provide a power of 95% with a 99% confidence interval using the following formula and considering the mean and standard deviation of intention to have based on the findings of a similar study by Moghaddam et al. [36]. The sample size was estimated at 12, and then considering 20% attrition, we plan to recruit 15 couples per group and a total of 30 couples study participants.$$n=\frac{{( {z}_{1-\frac{\alpha }{2}}+ {z}_{1-\beta } )}^{2} ({s}_{1}^{2}+ {s}_{2}^{2})}{{({\mu }_{1}- {\mu }_{2})}^{2}}=\frac{2.1664 \times 14.82}{2.6896}=\frac{32.106048}{2.6896}=11.93 \cong 12$$

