### Blinding

Additionally, there was no possibility of blinding the researcher due to the organization of the training sessions and the conduct of the interventions. However, medical center staff will be blinded. Blinding is also done when dividing the participants into two control and intervention groups and during the statistical analysis of the data. Training sessions for the intervention group will take place on days when people in the control group are not present at the clinic so that information is not randomly delivered to them and they do not communicate with each other. This issue will be the reason for the long process (about 2 years) of this research.

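### The attendance exclusion can act only after randomisation and only on intervention couples, so following it as written would bias the comparison if attendance is related to the primary outcomes

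*Protocol article*

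**What the plan says.** All places are in the protocol article.

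- **Exclusion criteria:** "Unwillingness to participate in the study, not attending more than one session, diagnosed infertility", followed by chronic disease that contraindicates pregnancy.
- **Order of events (Abstract, Methods):** "After collecting baseline data and separating participants in the pre-contemplation and contemplation stages based on the TTM, the samples were randomly assigned". Allocation therefore precedes any teaching.
- **Who is taught (Abstract, Methods):** "The intervention group will receive 60-min training based on TPB components for 4 weeks". No sessions are described for the control group.
- **How much teaching (Interventions):** "Teaching classes will be conducted in 4 sessions and each session will last at least 60 min".
- **Separation of the arms (Blinding):** "Training sessions for the intervention group will take place on days when people in the control group are not present at the clinic".
- **Follow-up (Data collection):** the questionnaires after baseline are completed online, and the researcher checks responses by telephone.
- **Analysis (Statistical analysis):** an ANOVA is named for effectiveness. The article does not say what becomes of the data of couples excluded for non-attendance.

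**The concern.** An exclusion criterion should be decidable before allocation, or should at least apply equally to both arms. This one does neither. A control couple has no sessions to miss, so the control group stays whole while the intervention group can lose its poorest attenders.

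Participants enter in the pre-contemplation or contemplation stage, and the primary outcomes are movement to later stages and a positive attitude to having a baby. It is plausible, though not shown in the document, that the couples least open to childbearing are the likeliest to skip sessions about it. Removing them would raise the intervention group's average even if the training did nothing. If they are also dropped from follow-up, their later outcomes are never collected, and no later analysis can restore them.

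**Working it through.** **1. Can the rule act before randomisation, or on controls?** Baseline data and stage screening come first, then allocation, then four sessions for the intervention group on days when controls are away. The attendance wording has two readings: missing two or more of the four sessions, or attending at most one. Under both, the rule can be applied only after allocation and only to intervention couples.

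**2. The plan's own figures (Sample size).** The printed formula gives 2.1664 × 14.82 / 2.6896 = 11.94 (printed as 11.93), so 12 per group, and 12 / 0.8 = 15. This agrees with "considering 20% attrition, we plan to recruit 15 couples per group". Taking 2.1664 as the sum of the two variances and 2.6896 as the squared difference:

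- common SD = √(2.1664 / 2) = 1.041
- planning difference = √2.6896 = 1.64
- standardised planning effect = 1.64 / 1.041 = 1.58 SD

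Whether the factor 14.82 matches the stated power is a separate question, which this point does not use.

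**3. Illustration of size.** The assumptions, none of them from the documents, are:

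- no true effect
- one normally distributed score per couple, 15 couples per arm
- the k intervention couples lowest on an attendance propensity are removed, and no controls
- correlation ρ between attendance propensity and score of 0, 0.3, 0.5 or 0.7
- two-sided t-test at 0.05, the article's significance level

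The expected bias in SD units is ρ × (minus the sum of the k lowest expected order statistics of 15 standard normals) / (15 − k). The three lowest are −1.736, −1.248 and −0.948.

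- k = 1: 1.736 / 14 = 0.124
- k = 2: (1.736 + 1.248) / 13 = 0.230
- k = 3: (1.736 + 1.248 + 0.948) / 12 = 0.328

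Multiplying by ρ gives the bias. Type I error comes from simulation with 60,000 replicates per cell.

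| Removed of 15 | Bias in SD, ρ = 0.3 / 0.5 / 0.7 | Type I error, ρ = 0.3 / 0.5 / 0.7 |
|---|---|---|
| 1 | 0.037 / 0.062 / 0.087 | 5.2% / 5.6% / 6.0% |
| 2 | 0.069 / 0.115 / 0.161 | 5.3% / 6.3% / 7.5% |
| 3 | 0.098 / 0.164 / 0.229 | 5.6% / 7.0% / 9.6% |

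With ρ = 0 the bias is zero and type I error stays at about 5%. Separate simulation runs differ by a few tenths of a percentage point. The rows are best read as about 5–6%, 5–8% and 6–10%.

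**4. Scale.** Against 1.58 SD, the smallest cell is 0.037 / 1.58 = 2% of the planning effect and the largest is 0.229 / 1.58 = 14%.

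**The case against.** Four objections deserve weight.

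- **The analysis set may be defined elsewhere.** A condensed article commonly leaves it to the analysis plan, and exclusion could mean only that a couple stops the classes. This stands in part: a reader might infer that the final comparison is certainly not between the randomised groups, and the article does not say so. But the item is listed as a study exclusion, so a later plan would have to override it, and it could not recover questionnaires that were never sent.
- **The size is assumed.** This stands. The 20% attrition is a general allowance for both groups, not a forecast of attendance exclusions in one arm. Three removed of 15 is therefore one scenario among several. No correlation is given. The primary outcomes are also a stage and an attitude, measured repeatedly. If change from baseline is analysed, the relevant correlation is with change.
- **The planning effect is large by comparison.** This also stands. A bias of this order would not by itself produce an effect of 1.6 SD.
- **Other exclusions might seem to share the fault.** A reader might infer that diagnosed infertility also acts after randomisation. Setting and participants ties it to previous medical records, and the inclusion criteria require no such history, so it is an entry check. If couples who began trying for a child were later diagnosed and removed, that would bias against the intervention. Nor does the point require every other exclusion to be confined to the time before randomisation. Participants may stop whenever they wish, and how an emerging contraindication is handled is a clinical matter outside this point.

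**Conclusion.** The point holds for the attendance criterion alone. The documents establish that it can act only after allocation and only in the intervention group. That it biases the result is conditional: couples must actually be removed under it, and attendance must be related to intention or attitude. Given both, the likelier direction favours the training. The size cannot be known from the article. Under the stated assumptions it runs from about 0.04 SD (one couple removed, correlation 0.3) to about 0.23 SD (three removed, correlation 0.7), with type I error between about 5% and 10%, and it is zero without correlation. That is modest against the planning effect but systematic, and neither the ANOVA nor a larger sample would remove it. It should be corrected because the rule is explicit and outcomes left uncollected cannot be restored.

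**What to change.** Delete the attendance item from the exclusion criteria and record attendance as adherence. Keep sending the post-baseline online questionnaires to couples who miss sessions, unless they withdraw. Analyse every randomised couple in the arm to which it was allocated. Use attendance only in a supplementary per-protocol analysis, and there state which of the two readings of the attendance rule is meant.

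The cost is a short amendment and a little more telephone follow-up, since responses are monitored by phone. The estimated effect may also be slightly smaller, because couples who received little training stay in the intervention group.

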### Interventions

After receiving the ethical code from the Research Center of Tehran University of Medical Sciences, the study will begin. The educational content of this study will be prepared under the supervision of specialized professors of the university and the researcher will acquire the necessary knowledge and skills to carry out the educational program under the supervision of professors. In preparing this content, we will try to include the following: Complications due to reduced population growth, factors affecting the reduced ability to have children, effects of reduced population growth on family and society, complications of pregnancy at older ages, effects of father's age, benefits of having children, economic effects of demographic decline. The choice of the content is based on: the educational needs of the couples reflected in the studies, the cultural problems of the society, and the subjects mentioned by the Ministry of Health of Iran. After the teaching materials are prepared, their contents are scientifically evaluated by the Tehran University of Medicine professors, and after their approval, the intervention and training process will begin. Teaching classes will be conducted in 4 sessions and each session will last at least 60 min with the presence of couples (Table 1).

**Table 1 Tab1:** The content of the educational sessions based on the theory of planned behavior

session	Main purpose	Educational materials	Educational methods and time schedule
1	Improving couples’ knowledge and attitudes toward	PowerPoint Booklet (including contents of all sessions) Pamphlet of the first session	1) Introducing presenter and participants and explaining study aims (10 min) 2) Giving information on effect of advanced ages on fertility capacity of couples and the pregnancy’s complications (40 min) 3) Question and answer (10 min)
2	Addressing the role of subjective norms in childbearing	PowerPoint Pamphlet of the second session	1) Reviewing previous session (5 min) 2) Giving information related to Islamic beliefs on childbearing and the importance of having a child on the religious and social perspectives of Iran (15 min) 3) Presenter will use the psychodrama method. In this method two female volunteer who have at least one child role‐play problems and release their intense emotions in regard to the child, then the presenter will guide their subjective norms (37) (30 min) 4) Question and answer (10 min)
3	Addressing the role of perceived behavioral control in childbearing	PowerPoint Pamphlet of the third session Video	1) Review of previous session (5 min) 2) Giving information on requirements and cares for becoming pregnant, prenatal cares, and care of newborn (30 min) 3) Presenting a short video which shows how a baby develops (5 min) Showing how to provide care during pregnancy and for newborn (10 min) 4) Showing videos of care of newborn (10 min) 5) Question and answer (10 min)
4	Addressing the behavioral intention and explaining how childbearing will change couple’s life	PowerPoint Pamphlet of the fourth session Video	1) Reviewing previous session (5 min) 2) Giving information on advantages of having a child from cultural, religious and social perspectives (10 min) 3) Showing videos of successful childbearing expression (10 min) 4) Question and answer (10 min)

Participants who meet the inclusion criteria will first complete a childbearing intentions questionnaire, which will be designed based on the stages of the change model and the samples who are in the pre-contemplation and contemplation stage will be included in the study. After this step, by accessing the Sib system “a national system that records health information of individuals”, couples who have been married for 2 years without children and meet the inclusion criteria will be selected. Then, 60 samples (30 pairs) will be selected through a random number table and will be randomly divided into 2 groups: control and intervention.

Teaching methods will include conferences, discussions, Q&A, and document distribution. During the classes, the researcher does not impose personal views and attitudes on the couple. It is explained to them that all decisions about having children are based entirely on their opinions and considerations and there is no coercion. They must also fill in the questionnaires without concern and honesty because their answers do not affect the quantity and quality of the treatment, and whenever they do not want to participate in the study, they can refuse to continue.

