### Statistical analysis

The analytical method used in this study will be quantitative. The information recorded in the questionnaire will be entered into the SPSS program at each stage and data analysis will be conducted after the research process is completed. Categorical variables will be reported based on frequency, and quantitative variables will be reported as mean (SD). The ANOVA test will be used for quantitative variables that have a normal distribution, and the Friedman test will be used for quantitative variables that do not have a normal distribution. The effectiveness of the intervention will be determined using an ANOVA test and the impact of demographic variables on factors measured using a logistic regression model. Statistical analyses will be performed using IBM-SPSS 22. For all analyses, P values  < 0.05 are considered statistically significant.

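### Couples appear to be taught together in classes in the intervention arm only, but the ANOVA and the sample size make no allowance for class; if couples share classes, the standard error is too small.

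*Protocol article*

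**What the plan says.** The abstract states that thirty couples, 15 per arm, "will be enrolled in this cluster randomized controlled trial". The Interventions section has "60 samples (30 pairs) will be selected through a random number table and will be randomly divided into 2 groups", so the couple is the only cluster that the text identifies.

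On delivery, the same section says "Teaching classes will be conducted in 4 sessions and each session will last at least 60 min with the presence of couples". Table 1 opens session 1 with "Introducing presenter and participants and explaining study aims", and later text adds "Teaching methods will include conferences, discussions, Q&A, and document distribution". The Blinding section confines the teaching to one arm: "Training sessions for the intervention group will take place on days when people in the control group are not present at the clinic". No class is described for controls.

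On analysis, the Statistical analysis section says "The effectiveness of the intervention will be determined using an ANOVA test", at a significance level of 0.05. The Sample size section uses the formula for two independent means, with no design effect. Neither section mentions class, and the number and size of classes appear nowhere in the article.

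**The concern.** Couples who sit through the same sessions share a discussion, a set of questions and a group mood. Their later answers may therefore be more alike than those of couples taught apart. Subjective norms are a taught target and attitude is a primary outcome, and both are open to influence from classmates. Control couples have no such grouping. This is a partially nested design, with correlation between couples in one arm only.

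An ANOVA without a class term counts every intervention couple as independent information. Any positive class correlation then makes the standard error of the arm difference too small and the false-positive rate too high. This level lies above the couple, so it would remain even if the two spouses were reduced to one value per couple. With a single class there is a further problem: one unusually lively or unusually cool group cannot be told apart from an effect of the course. The Discussion hopes that national policy will draw on the results, so an honest error matters.

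**Working it through.** **The plan's own figure.** The Sample size section gives 2.1664 × 14.82 / 2.6896 = 11.94 (printed as 11.93), so 12 per group. Allowing for 20% attrition, 12 / 0.8 = 15 couples. The multiplier 14.82 equals (2.57 + 1.28)², so 2.1664 is read as the sum of the two variances. The planning effect is then √2.6896 / √(2.1664/2) = 1.64 / 1.041 = 1.58 SD. (That multiplier corresponds to two-sided alpha 0.01 with 90% power, not the stated 95%; this is a separate matter.)

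**Assumptions.** Class size m (couples per class) and class ICC are not in the document. The range used is m = 3, 5 or 15 and ICC 0.01 to 0.20, with one value per couple and 15 couples per arm.

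**Formula.** The variance of the intervention mean is multiplied by DE = 1 + (m − 1) × ICC; the control mean is unaffected. Hence

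true SE / unadjusted SE = √((DE + 1) / 2).

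Examples:
- m = 3, ICC 0.05: DE = 1.10, ratio √(2.10/2) = 1.025.
- m = 5, ICC 0.10: DE = 1.40, ratio √(2.40/2) = 1.10.
- m = 15, ICC 0.10: DE = 2.40, ratio √(3.40/2) = 1.30.

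**Type I error of the unadjusted two-arm test at nominal 5%** (simulation, 40,000 trials per cell; couple values with total variance 1, class variance equal to the ICC in the intervention arm only):

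| Classes | ICC 0.01 | ICC 0.05 | ICC 0.10 | ICC 0.20 |
|---|---|---|---|---|
| five of 3 couples | 5.0% | 5.6% | 6.1% | 7.4% |
| three of 5 couples | 5.2% | 6.0% | 7.4% | 9.7% |
| one of 15 couples | 5.9% | 9.2% | 13.8% | 22.2% |

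Repeat runs move these entries by a few tenths of a percentage point. With m = 1 or ICC = 0 there is no inflation.

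**With class respected.** Comparing intervention class means with control couple means, using Satterthwaite degrees of freedom, gives a type I error of 5.0 to 5.3% with five classes and 5.4 to 6.0% with three. With one class the variance between classes cannot be estimated, so no such test exists.

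**Effect on the planned size.** On the plan's own multiplier, the 12 per group becomes 12 × (DE + 1)/2. For m = 5 this is 12 × 1.10 = 13.2 at ICC 0.05 and 12 × 1.20 = 14.4 at ICC 0.10. After 20% attrition these are 13.2 / 0.8 = 16.5 and 14.4 / 0.8 = 18 couples per group, against the planned 15. This leaves out the further loss from having few degrees of freedom.

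**The case against.** The strongest reply is that group teaching is inferred. No sentence gives the number of classes or the couples per class. The session 1 item does not say that couples are introduced to one another. The psychodrama is played by women who already have a child, so it is not interaction among trial couples. A training period of about 2 years would also fit several small classes. All of this stands as a limit on certainty. It does not overturn the reading: classes, discussions and an introduction of participants describe group teaching far better than one couple at a time.

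Second, a reader might infer that the standard errors on every outcome are certainly too small and that the false-positive rate certainly exceeds 5%. The document does not support that. Both statements depend on a class size and an ICC that it does not give. With small classes and an ICC of 0.01 the inflation is negligible. The large figures need all 15 couples in one class and an ICC of 0.10 or more. A single researcher delivering prepared, expert-reviewed content also removes variation between teachers, though not influence among classmates.

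Third, the article is condensed, and a full analysis plan might add random terms. That is fair as regards the model's details. But the article does name the effectiveness test and print the sample-size formula, and neither allows for class. The number of classes is a matter of design: a later analysis plan cannot undo a single class.

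Finally, correlation between spouses is a separate and probably larger problem, and the article does not say how it is handled. That is true, but solving it would leave the class level untouched.

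**Conclusion.** The point holds in conditional form. If more than one couple shares a class and the class ICC is positive, the stated ANOVA understates the error and the sample size is somewhat too small. The direction is certain under those two conditions. The size rests on the assumed class sizes and ICCs: slight to moderate with classes of three to five couples, and potentially serious with one class of 15. In the single-class case the defect lies in delivery rather than in the test, because no analysis can separate class from course. The matter should be settled before training starts, since class membership and the number of classes cannot be repaired afterwards.

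**What to change.** 1. State how many classes will be run and roughly how many couples each will hold. Spread the training, already planned over about 2 years, across several classes rather than one. Five classes of three is an example, not a requirement.
2. Record each intervention couple's class as a variable.
3. Make the main comparison with the couple as unit and a class effect in the intervention arm only, using Satterthwaite or Kenward-Roger degrees of freedom. Alternatively, compare intervention class means with control couple means using Satterthwaite degrees of freedom. Name one of these in advance: they need not agree when class variance is estimated from three to five classes of unequal size, and only the class-means test was simulated here.
4. Add the class design effect to the sample size, with the assumed ICC stated.
5. If only one class is run, say in the protocol and the report that the result cannot separate class from course.

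**Cost.** One variable, one model term, some repeated sessions and lower power. At 1.58 SD and ICC 0.05, unadjusted test against class-means test:

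| Setting | Unadjusted | More classes | Three classes |
|---|---|---|---|
| 15 couples per arm, alpha 0.05 | 98% | 96% (five) | 88% |
| 12 completers per arm, alpha 0.05 | 96% | 90% (four) | 83% |
| 15 couples per arm, alpha 0.01 | 93% | 82% (five) | 65% |

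The unadjusted column is not a fair benchmark, because part of that power comes from a test that rejects too often. The planning effect is also large. At 0.8 SD, with 15 couples per arm and alpha 0.05, power is 56% unadjusted and about 49% (five classes) or 43% (three) on class means. More, smaller classes lose less power.
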